#### Interviews and observations

The aim of the semi-structured interviews and observations was to obtain detailed, qualitive information on the disruptions, interruptions, and information overload related to the work tasks of participants. Stress management, recovery, balance between work and leisure time, and the resources that support work performance were also covered. The focus of the interviews and the observations was to determine the participants’ general work characteristics (working time in terms of ICT, meetings, and other tasks) and typical tasks at work. We observed both challenges to and good solutions for performing cognitively demanding work tasks, as well as situations that affect cognitive strain, workload and recovery. Interviews and observations were conducted either at the participant’s desk or, if they worked in an open office, in a meeting room. Each session took about 1.5–2 h. Seven interviewers – psychologists who were trained in the use of the method (including VK, SS, and HJ, and one graduate student of psychology who was completing obligatory clinical training) – conducted the interviews and observations.

Before giving their written consent, the participants received both oral and written information on the study, interview, and observation. The semi-structured interview started with a few minutes of information on the contents of the interview, followed by a 20- to 30-min background interview on education and work experience, work tasks, and the demands and settings of work. The next stage included a 45- to 60-min observation of the participants’ typical work tasks. Participants had been instructed to think aloud and explain what they were doing. Depending on their work, we focused on 3–7 typical tasks, sometimes some more important common tasks. In the end, a short interview completed the information on the conditions related to strain, workload, engaging factors, and recovery, and enabled a discussion on anything the interviewee wished to add or ask. If the interviews and observations were conducted in a meeting room, a short visit to the participant’s office or desk was also included to obtain information about the actual work environment.

#### Cognitive ergonomics intervention at the workplace, CogErg

The intervention method, Cognitive Ergonomics Intervention Programme at the Workplace (CogErg), has been developed at FIOH in recent years in cooperation with various organizations and occupational health and organizational psychologists. The programme was refined and described in detail in the study intervention manual (version 2018-02-06, available in Finnish) for both the cognitive ergonomics intervention (treatment) and equivalent recovery support intervention (active control), before the start of the intervention. The intervention includes two steps: 1) the initial workshop, and 2) providing support during the implementation phase. The intervention is carried out in an authentic work context in co-operation with the employees, and the focus is on the work community level, that is, teams and other organizational groups working together.

The basic idea of CogErg is that the work community develops shared, good and concrete practices to improve cognitive ergonomics, and implements these practices in their daily work. The intervention thus aims to enhance group-level behaviour change, demonstrated as improved cognitive ergonomics in work and working conditions. The intervention applies the Mental Contrasting with Implementation Intentions (MCII) behaviour change method [44], utilizing its basic elements: first, the contrast between the current situation and future goals is demonstrated and, second, during the workshop and the implementation stage, concrete IF–THEN ground rules for work are defined. Furthermore, the workshop exercises and the reminders during the intervention implementation phase use the WOOP elements of the MCII method, that is, Wish, Outcome, Obstacle, and Plan [44].

#### The intervention workshop

The intervention starts with a workshop, organized either as one, two, or three equally long sessions, totalling three hours. The workshops are organized 4–8 weeks after the baseline survey, and the timeline is tailored for the participating organization. All participants are either present, or participate in the sessions via an electronic meeting system (e.g. video conference call). The treatment and active control groups participated in similarly structured workshops, but the specific content was different. The structure and content of the workshops are presented in Table 4.

**Table 4 Tab4:** Outline of cognitive ergonomics and recovery support workshops

Phases	Description	Examples
Introduction of workshop	Presentation of workshop goals and information on the topics according to group allocation	Topics CE: 1. Disruptions, 2. Interruptions, and 3. Information overload.
		Topics RS: 1. Stress management, 2. Recovery, and 3. Work-life balance
MCII: Optimal situation vs results of baseline measurement	Optimal situation based on research evidence vs organization’s current situation according to questionnaire, interviews and observations.	Same structure for both intervention arms.
Informed consent	Oral and written information on the study, signed informed consent. If all participants agree, the workshop discussion during the second part is recorded	Same structure for both intervention arms.
Task assignment and groupwork (3–4 persons/group)	Planning practices to improve current situation under intervention arm topics. The group chooses a spokesperson as well as a record-keeper, who keeps the schedule and saves the group’s answers on a structured intervention sheet.	Same structure for both intervention arms.
WOOP method:		
Wishes (W) and Outcomes (O) (10 min)	Wishes and optimal outcomes are sketched for the group. Group discussion: i) importance of issue in the work community ii) indication whether issue is in order or resolvable and iii) other comments and questions	CE: “There isn’t too much noise, and speech is muted: there are no unnecessary distracting ringtones or movement (W); we have agreed on ground rules and working methods that reduce noise and distractions (O).”
		RS: “The strain factors are in balance with resources at work; the amount of strain at work is appropriate (W); We have agreed on ground rules and working methods that help us manage strain (O).”
Obstacles (O) (10 min)	Naming the concrete obstacles (e.g. situations) that prevent the achievement of outcomes and how to deal with them.	CE: Discussion and identification of distractions that hinder work and flow of tasks, such as speech, noise, and people passing
		RS: Discussion and identification of specific working conditions that increase strain, such as situations resulting in lunch breaks being skipped
Plan (P) (50 min)	Formulating ground rules (GR) and describing the working method by using IF-THEN rules, arguing why the issue is important (I) to the group, and discussing how the group can make the change (C) work together. Working with both ready-made examples and own rules describing the working methods.	CE: “We’ll control our voices”. IF I work in a space where there are other people, THEN I will lower my voice and keep the noise level low. (GR) “In many spaces noise is a major straining factor, every one of us can affect the noise level around us” (I). “Person X will bring the issue up in a team meeting” (C).
		RS: “Schedules are predictable”. IF unpredictable tasks arise often, THEN there is time reserved in the calendar for them. (GR) “Scheduling time for unpredictable tasks reduces haste and time pressure” (I). “Supervisor Y ensures that the matter moves forward” (C).
Utilization and dissemination (5–10 min)	Consideration of concrete implementation of behaviour change methods to ensure success. Structured evaluation i) of the usefulness of the workshop and ii) of the engagement in the behavioural change.	Concrete methods for both intervention arms; for example, what things should be further discussed and with whom; what message needs to be passed on, how and to whom; what long-term measures should be undertaken
Conclusion	Discussion and sending of files to research contact person.	Same structure for both intervention arms.

*MCII* Mental Contrasting Implementation Intentions, *WOOP* Elements of the MCII method, Wish Outcome, Obstacle, and Plan, *GR* Ground rule, *I* why the issue is important, *C* how the group can make the change, *CE* Cognitive Ergonomics group, *RS* Recovery Support group

The first part consists of an introduction, which describes the goals of the workshop and information on the three focus themes based on intervention group allocation (cognitive ergonomics, CE, or recovery support, RS), and the key results of the baseline survey and the interviews. The presentation material is then framed to reveal the mental contrast between an optimal situation and the current situation in the work community. We present the results by showing that the optimal situation based on research knowledge on workplace well-being and productivity is not yet realized in the work community.

The next part focuses on planning good, concrete practices that improve the current situation under the three main themes of the workshop. Participants work in groups and are provided with detailed instructions for discussion and a questionnaire that supports developing the work community’s common working methods under the intervention themes (CE or RS).

The workshop tasks follow the WOOP method of MCII. In the first tasks (about 10 min) the Wishes, that is, the three themes of the workshop, are named and the optimal outcomes are sketched for the group. The idea of this task is to enhance mental contrasting by realizing and discussing the current situation and any possible outcomes, and to increase commitment to the wishes and outcomes.

The second workshop task (about 10 min) focuses on obstacles, and the group is instructed to discuss concrete situations in which workflow suffers. The idea of this task is to help the group notice the obstacles to the outcomes. It is important to notice that our study focuses on the obstacles related to working conditions and working methods, rather than inner mental obstacles, which are the focus of other studies applying WOOP or MCII (see for example [44, 45].

The third workshop task (about 50 min) is about developing ground rules. The aim of this task is to develop concrete working methods that lead to outcomes, and to formulate them as organization-specific IF–THEN rules to enhance behaviour change. Two examples are given for each theme, and the group is asked to assess how suitable the named working method is for them. The examples are tailored to be relevant to the participating organization and are based on the material obtained from the baseline interviews and observations.

The fourth workshop task (about 5–10 min) for the group is to discuss and assess how they can ensure success and prepare to bring their view to the joint final discussion of the workshop. The idea of the fourth task is to increase commitment to and activity during future steps.

The workshop ends with a short joint discussion that brings together some ideas from different sub-groups that joined the workshop and provides information on the next steps of the study. The workshops are delivered by four psychologists and three specialist/researchers (including VK, HJ, TV) who are trained to present the material and lead the workshop.

#### Intervention task reminders

The implementation phase starts 2–12 weeks after the workshops in the organization and the time line is tailored for the participating organizations. All employees of the participating units receive an email once or twice a week containing short task questionnaires that take about five minutes to complete during working hours. Altogether 10 task reminder questionnaires are sent to the employees and supervisors, and three questionnaires are sent to the supervisors only. The task questionnaires remind participants of the issues agreed upon, ask how well the ground rules work in practice, and include some items related to presence and well-being at work (see Table 1). The purpose of these short questionnaires is to support the implementation of the new working methods and the ground rules agreed on during the workshops. The structure of these reminders is the same for the treatment and the active control group, but the content follows the themes relevant to each group. Furthermore, the good practices named in the workshop task replies of each organization are formulated to organization-specific IF–THEN rules, making also the examples and detailed content in the intervention task reminders organization-specific.

#### Evaluation workshop

Evaluation workshops will be arranged for each of four organizations between the end-of-treatment and follow-up surveys, and separately for the Cognitive ergonomics (treatment) and the Recovery support groups (active control). The evaluation method is interactive and learning-oriented, and combines the benefits of participatory and external evaluation by applying an aquarium method and a multi-criteria evaluation framework that supports multi-voiced evaluation (described in more detail in [46, 47)]. There are six dimensions for evaluating the impacts of the service innovation (in our study, the impact of the intervention): impacts on the citizen, the employee, and the population; and impacts on reputation, integration of technology and services, and economy.

The length of each evaluation workshop is 2–3 h. Participants sit in two circles and discuss and evaluate the success of the implementation of the intervention and new ways of working. The inner circle consists of 3–8 members who have participated in the intervention implementation phase, and they are asked to first discuss and evaluate the six dimensions of the intervention. The outer circle, with 3–6 members (e.g. managers, well-being/safety specialists, others who have not participated in the intervention) listen carefully and then comment on the discussion and suggest concrete actions for going forward.

### Tailoring

The detailed content of the CogErg intervention and the detailed timeline of the intervention’s implementation are tailored to suit the participating organizations. However, the three focus themes, the structure of the workshop and the structure of the implementation are constant and the same for all the participating organizations. In the workshop, the detailed content of information is tailored for the organization in question, that is, the baseline results of the survey and the interviews/observations, and the IF–THEN rules that are given as examples in the workshop tasks. Furthermore, the good practices named in the workshop task replies of each organization are formulated into organization-specific IF–THEN rules, making also the examples and detailed content of the intervention task reminders organization-specific.

The tailoring of the implementation of the measurements and intervention has the following components: whether the organization invites all or only a selection of employees to the workshop; whether the three-hour workshop is arranged as one, two or three sessions; and whether the workshop is arranged live or held via a technological communication system. Furthermore, organizational situations (such as busy periods, holiday periods, communication culture) may affect the exact timing of the intervention task reminders, as may as the number of reminders sent to participants that have not responded to the survey and questionnaires. Activities for communicating with the organization are tailored to their needs.

### Outcome measures

The outcome measures are based on the study questionnaires presented in Table 3. The items of the measures are presented in Table 2. The primary outcome measure of the study is Cognitive Strain Prevalence, the average of three subscales: Disruptions, Interruptions and Information Overload. The subscales are weighted averages of items from the Brain Work Profile and Knowledge Work Cognitive Failure Scale questionnaire modules. The participants are asked to “*Think of your work over the last month and for each question, mark how often your work required you to do the things presented*”. For example, “*Work in a noisy environment or with speech in the background?*” (Disruptions); “*Interrupt a task that is underway?*” (Interruptions); or “*Monitor several things and observe changes?*” (Information overload). The items are assessed for the frequency of dealing with the named cognitively demanding working conditions on a five-level scale: Multiple times per day, Daily, Weekly, Monthly, or More rarely. Responses are transformed into times-per-week values (10, 5, 1, 0.22 and 0 times per week, respectively) to approximate a continuous variable for calculating the averages. When counting the subscale averages at each study phase, the variables are weighted by their factor loadings in the baseline survey.

We also analyse the effect of the treatment on several secondary outcome measures, described in Table 2. The Subjective Cognitive Strain measure includes the same 15 items as the Cognitive Strain Prevalence measure, but the items assess subjective strain on a six-level scale: Energizing – a lot, Energizing – quite much, Energizing – a bit, neither energizing nor straining, straining – a bit, straining – quite much, straining – a lot. Second, we also use all 39 items from the Brain Work Profile questionnaire module as a measure of general Subjective Cognitive Strain. There are 13 cognitive categories, including the Cognitive Strain Prevalence items, but also items related to language processing, visual demands, problem-solving, and other cognitive demands. The question in this measure is “*You answered that your work requires you to do the following at least monthly. How do you feel about these things*? Do they motivate / energize you, or do they cause you strain?”. Examples of items included in this measure are “*Read or write instructions, messages or documents?*” (Language); “*Be able to see small visual details?*” (Visual); and “*Find alternative solutions?*” (Problem solving).

Well-being includes four measures. Subjective stress is measured with a stress-symptoms item that has shown satisfactory content, criterion, and construct validity for group-level analysis [48]. The experience of stress is assessed on a scale of 0 to 10: “*By stress we mean a situation in which a person feels tense, restless, nervous, or anxious, or they find it difficult to sleep because they cannot switch off their thoughts. Do you currently feel this kind of stress?”* A similar recovery item is assessed on a scale of 0 to 10: “*How well do you usually feel that you recover from the strain caused by your work (both mental and physical) after your working day/work shift?*”. Our General Health measure is a single item from the COPSOQ-II questionnaire [41, 42] and our Burnout measure the four-item COPSOQ-II Burn Out index (Cronbach alpha 0.83), including, for example, the item “*How often have you felt worn out?*“.

Cognitive Stress Symptoms (Cronbach alpha 0.83) is also a measure of the COPSOQ-II questionnaire [41, 42], including, for instance, the item “*How often have you had problems concentrating?*“.

Work Flow and Productivity measures include four measures. Presenteeism and Subjective Productivity measure includes “*How would you rate your own everyday performance during the last one or two years?*” [39]. The three Cognitive Failure measures are assessed for “*How often does the following happen to you in your work?*”, for example, “*You do not remember a password, numerical series, etc. that you need for your work*” (Memory Failures Measure); “*Your attention easily turns from your own work to your colleagues or what they are doing*” (Attention Failures Measure); and “*You find it difficult to decide which of several tasks is the most important to complete*” (Multitasking Failures Measure). Memory and Attention Failure measures are adapted from the Cognitive Failure Scale which shows high factorial, construct, and criterion-related validity [49].

## Plan of analysis

The analyses will include primary and secondary outcome analyses, post-hoc analyses, qualitative analyses, and process evaluation. The results will be reported in multiple articles dedicated to specific aspects of the study.

### Outcome analyses

The primary outcome variable is Cognitive Strain Prevalence (see Table 2). Descriptive statistics (frequencies, means and SD), the Mann-Whitney U-test, and chi-squared test will be used for baseline, end-of-treatment, and follow-up (4 month and 10 month) data to determine whether participant and group characteristics are comparable in the treatment and active control groups (randomized groups) and the passive control group (non-randomized group). The main longitudinal data analyses will be based on the Linear Mixed Modelling procedure, including incomplete cases in the analysis and assumes that missing data are random. The data are naturally hierarchical and consist of four organizations, organizational units (clusters), and individual respondents. Organization- and individual-level factors (e.g. gender and age) are included in the model, and the main level of the primary analyses will be that of the cluster. Item-level missing or invalid values are expected to be few, due to the computerized response format, and are not replaced.

Furthermore, additional analyses will include the non-randomized passive control group data in the baseline and end-of-treatment phases. Additional primary outcome analyses will also include post-hoc analyses with possible moderators in the model. The moderators will be defined on the basis of the process evaluation analyses.

Secondary outcome analyses will be the same as for primary outcome measure. We will also analyse subjective productivity measures using difference-in-difference regression. Additional post-hoc analyses such as mixed graphical models or trajectory analyses will also reveal, for example, the factors that predict successful change in a group.

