### Sample size

We assumed that all employees would meet the inclusion criteria, and that at least 60% of the participants invited to the baseline survey would respond. It was further assumed that the follow-up attrition would be less than 50%. The meaningful significant difference estimation was calculated on the basis of sub-group differences in previously collected unrelated data (*N* = 2154) on cognitively straining working conditions. The sample size estimations were based on the average size of the teams; we could not define a fixed group size as the clusters in this study are real organizational units that vary in size. According to the power analyses, 32 groups with 15 eligible participants in each is the estimated sample size required to achieve a statistical power of 0.95 with an alpha of 0.05, if the ICC (intraclass correlation coefficient) is assumed to be 0.3 (For detailed information on how group size and ICC affect power, see [43]). Thus, to achieve a significance level of 0.05 when requiring 0.95 power, a sample size of *N* = 480 participants (15 per group) is needed to enable finding a significant difference in the primary outcome of the different arms. A follow-up attrition of 50% and a baseline response rate of 60% would require inviting altogether 1600 participants in order to meet the power requirements defined above. If power was set to 0.80, the required sample size would be 330.

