The main research question of our study is whether a cognitive ergonomics intervention can reduce the frequency of cognitive strain in working conditions. However, we will also analyse whether the intervention affects subjective performance and well-being. The results will also provide information on the effects of recovery support intervention and will clarify whether the outcomes of the intervention that focuses on reducing cognitive strain in working conditions and ways of working are different to those of the intervention that supports recovery. Thus, our study combines the research field that focuses on job design and job crafting for improving work performance and the research field of employee well-being and its consequences. The results will contribute to the current discussion on whether productivity and well-being at work have mutual connections, that is, the happy worker-productive worker thesis [19].

However, certain limitations deserve attention. Our study approaches groups of employees within the organization, and the intervention includes both individual and organizational level elements. The participative elements during the workshop and implementation aim to commit individual employees and supervisors and support behaviour change among individuals within the groups. On the other hand, the focus is on common working conditions, and related changes require organizational-level commitment and decisions. Thus, successful implementation would require actions on both the individual and organizational level. Selection bias within the groups may result if those who volunteer to participate in the study condition are more interested in the named themes than the non-participating employees. For example, those motivated to change working conditions may be overrepresented in the treatment group, whereas in the active control group, the participants motivated to enhance recovery may be overrepresented and more active during the implementation phase. This kind of selection bias could also increase if the basic level of the primary and secondary outcome variables differs between the participating individuals in the groups, despite randomization.

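### The Mann-Whitney and chi-squared comparability tests make no allowance for clustering, so on participants in the two randomized arms they reject more often than 5%

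*Protocol article*

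**What the plan says.** The Outcome analyses section of the protocol article states that, besides descriptive statistics, "the Mann-Whitney U-test, and chi-squared test will be used for baseline, end-of-treatment, and follow-up (4 month and 10 month) data". The stated purpose is "to determine whether participant and group characteristics are comparable in the treatment and active control groups (randomized groups"), together with the non-randomized passive control group. No unit of analysis and no adjustment for clustering is given for these tests.

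The same paragraph recognises the structure of the data: "The data are naturally hierarchical and consist of four organizations, organizational units (clusters), and individual respondents". For the outcomes it acts on that: "The main longitudinal data analyses will be based on the Linear Mixed Modelling procedure", and "the main level of the primary analyses will be that of the cluster".

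The Study design and Randomization sections say that whole work units were allocated within four organization strata. Clusters were ordered on the stratification factors, and a random number decided whether the odd or the even ones received the treatment. The Sample size section gives the article's only intraclass correlation, in the power calculation for the primary outcome: "if the ICC (intraclass correlation coefficient) is assumed to be 0.3".

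**The concern.** Mann-Whitney and chi-squared tests take every respondent as an independent observation. Members of one work unit went to the same arm together. If they resemble each other on a characteristic, the difference between arms varies more by chance than these tests allow, and their p-values are too small.

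At baseline this matters in a simple way. The Randomization section used first-survey response in the stratification, so the baseline survey came before allocation. A baseline difference between the two randomized arms is therefore chance, and a significant result is a false alarm.

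What is at stake is the statement of whether the arms are comparable. The Discussion gives that statement some weight, since it warns that "This kind of selection bias could also increase if the basic level of the primary and secondary outcome variables differs between the participating individuals". A test that often flags ordinary unit-to-unit variation is a poor guide to that question.

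**Working it through.** **The plan's own figures.** The article gives no error rate for the comparability tests, so none can be reproduced. Its sample-size arithmetic does reproduce: 32 × 15 = 480, and 480/(0.60 × 0.50) = 1600 invitations. The power claim itself (32 groups of 15 for 95% power at the 5% level) cannot be reproduced, because no effect size or standard deviation is stated. It is used here only as the source of the ICC and the planned cluster size.

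**Inputs**
- 36 randomized clusters and 638 valid baseline responses (240 + 144 + 153 + 101), from the Participants section. Mean m = 638/36 = 17.7.
- ICC 0.3, from the Sample size section (primary outcome). No ICC is given for age, gender, education or length of employment, so 0.01, 0.05 and 0.10 are assumptions chosen to show the range.
- Follow-up: m = 319/36 = 8.9. This is an assumption. It halves the baseline sample, whereas the article expects attrition below 50% and adds new employees at later phases.

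**Formulas**
- Design effect: DE = 1 + (m − 1) × ICC
- True two-sided size of an unadjusted nominal 5% test: 2 × [1 − Φ(1.96/√DE)]

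Example at m = 17.7 and ICC 0.3: DE = 1 + 16.72 × 0.3 = 6.02; 1.96/√6.02 = 0.80; size = 42.4%.

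| ICC | DE, m = 17.7 | Size | DE, m = 8.9 | Size |
|---|---|---|---|---|
| 0.01 (assumed) | 1.17 | 7.0% | 1.08 | 5.9% |
| 0.05 (assumed) | 1.84 | 14.8% | 1.39 | 9.7% |
| 0.10 (assumed) | 2.67 | 23.1% | 1.79 | 14.3% |
| 0.30 (planning value) | 6.02 | 42.4% | 3.36 | 28.5% |

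At the planned 15 per cluster and ICC 0.3, DE = 1 + 14 × 0.3 = 5.2 and the size is 39.0%.

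**Allowing for the restricted allocation.** The formula ignores stratification. A simulation used 36 clusters in four strata, unequal cluster sizes, clusters ordered by size within organization, and random odd/even allocation, with 1500 runs per setting. The clusters per stratum (14/8/8/6) and the coefficient of variation of cluster size (0.5) are assumptions. The chi-squared test used the same trait cut into two categories. Results at baseline, ICC 0.3:

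| Share of between-cluster variance lying between organizations | Mann-Whitney on participants | Chi-squared on participants | Mann-Whitney on cluster means |
|---|---|---|---|
| None | 48% | 38% | 4.1% |
| Half | 35% | 28% | 1.9% |
| 90% | 14% | 11% | 0.1% |

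At ICC 0.05 the participant-level sizes were 15% and 13% with no organization share, 11% and 9% with half, and 7% and 7% with 90%. At ICC 0.01 they were about 5-6% throughout. Balance on task type was not simulated; it would work in the same direction for traits that follow task type.

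**The case against.** **The article does not say that the tests are run on individuals.** It covers participant and group characteristics and names no unit, and a condensed article may leave that to a fuller plan. This stands in part. A test of a true cluster attribute on 36 units is not inflated by within-cluster correlation. But the sentence also covers participant characteristics, and the Background module collects age, gender, education and length of employment from individuals. The named tests, run on such data as written, count respondents.

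**The 42% borrows an ICC meant for the primary outcome, and the formula ignores stratification.** This stands. A reader might infer that every characteristic would be falsely flagged about four times in ten. The article gives no ICC for demographics, inflation is slight at 0.01, and balancing on organization and task type lowers it for traits that follow them.

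**The consequences can be overstated.** A reader might infer that these tests are the plan's way of detecting selective dropout or of choosing covariates. The text says neither. It describes no responder analysis, attaches no decision rule to the p-values, and already puts organization- and individual-level factors in the model. The selection-bias passage in the Discussion mentions no test.

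**No true null holds everywhere.** This also stands. The passive group was not randomized, so real differences may exist there. After baseline, differences between the randomized arms may also be real.

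**Conclusion.** The point holds for one use: the named tests applied to participant characteristics in the two randomized arms. There they ignore the clustering that the same paragraph acknowledges, and they reject too often. At 17.7 respondents per cluster the true size of a nominal 5% test is about 7% at ICC 0.01, 15% at 0.05 and 23% at 0.10. For variables that behave like the outcome it is up to about 42% by the formula at ICC 0.3. In simulation at ICC 0.3 it was roughly 11-35% where half to 90% of the between-cluster variance lay between organizations.

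These figures rest on assumed ICCs for everything except the primary outcome and, in the simulation, on assumed cluster counts per stratum and assumed size variation. The follow-up figures also assume that half the baseline sample responds.

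It would be wrong to read this as a fault in the primary analysis. The linear mixed model recognises the hierarchy and is untouched. The flaw is confined to the statements about comparability.

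**What to change.** Change the sentence in the Outcome analyses section so that:
- participant characteristics in the randomized arms are described by arm at each survey with summaries and standardised differences, without unadjusted tests;
- where a test is wanted, it is a cluster-level comparison or a mixed model with work unit as random effect and organization as fixed effect;
- unadjusted Mann-Whitney and chi-squared tests are kept only for cluster-level characteristics, with the cluster named as the unit of analysis.

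Organization should be accounted for in any such test. In the simulation, a plain Mann-Whitney test on cluster means held its level when organizations did not differ, but became very conservative when they carried most of the variance.

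The cost is a sentence in the plan, a changed table and slightly more analysis work; no new data are needed. The downside is that the balance tests become less sensitive, because they then rest on 36 units rather than on 638 respondents.
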